**12c. Safety considerations/Patient safety**

PBMt is considered a safe treatment. In over 50 years of research on the effects of PBM, there have been no published results of harm when used within the correct dose window. Dosing protocols for the PD trial have been based on both clinical experience by members of the research team ([name]) and others (Videnovic et al., 2017), as well as results of PBMt studies in primates and mice (Darlot et al, 2016). No side-effects of PBMt or safety concerns using PBMt, have been reported in either of the two previous arms of the PD trial performed in Brisbane and Adelaide.

**13. DATA ANALYSIS**

**13a. Outcome measurements**

Baseline data for all outcome measures collected before the beginning of treatment will form the reference point for analyses.

**13b. Statistical analysis**

As a series of N=1 studies, it is anticipated that only basic statistical analysis will be performed. For each outcome measure, descriptive data (mean, standard deviation) will be calculated. From this data, “minimally important difference” (MID) scores will be computed based on ½ SD of each measure. This is a common MID measure (Norman et al, 2003) based on the distribution of the participant scores at baseline and provides a sensitive indicator of significant change over time for N=1 case studies. As such, it does not suffer from a lack of statistical power that would be evident with more traditional ANOVA approaches with small sample sizes. The number of participants showing improvement (i.e., difference between two time points > MID) can be compared between time points with chi-square analyses.

Participants showing improvement in the Sydney arm of the multi-centre Parkinson’s trial will be compared to the Brisbane and Adelaide arms (chi-square analysis) in order to establish optimum PBM areas of treatment and doses regimens.

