The Sydney proof-of-concept trial follows on from proof-of-concept trials which have been completed in Brisbane and Adelaide. The Brisbane trial was a randomised placebo trial using transcranial photobiomodulation and showed significant differences between the treated and placebo group. The Adelaide trial was a waiting-room design with transcranial, intranasal, cervical spine and abdominal photobiomodulation; results are still being analysed but look very encouraging, including potentially positive changes in the microbiome. The Sydney trial will be a case-matched trial and use abdominal and cervical spine photobiomodulation only. The Sydney trial will be conducted over a 12-week treatment period and will assess a number of outcome measures, including motor abilities, cognitive function, microbiome changes, cytokine levels and potential Parkinson’s disease marker changes, as well as self and carer assessments of wellness. The trial is to be conducted in two stages: an initial cohort will be assessed in September, to begin treatment in October. A further cohort will begin treatment in August 2021. The funding for the Sydney trial has been provided by the San Foundation and from private donors. Additional funding ($27,000) has been obtained to conduct the second stage of the trial. The results from all three trials will be used to argue for a large-scale, randomised, double-blinded trial.

The idea for this study emerged after a previous study evaluating the application of photobiomodulation in participants with PD was completed (approved by Griffith University HREC). Ethics approval for this study is being sought through the AHCL HREC. This study will be a simplified blinded placebo/sham-controlled trial with the following sites:

- Northshore Musculoskeletal and Laser Physiotherapy Clinic, [name].
- Photobiomodulation Clinic, Specialist and GP Centre, San Hospital, [name]
- [name], San Hospital, [name]

The sponsor and the supplier of devices for this study will be SYMBYX Biome Pty Ltd, [name]

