**5. HYPOTHESIS**

5a. Primary Hypothesis: PBMt will have no adverse effects on PD participants

5b. Secondary Hypothesis: PBMt will reduce the symptoms of PD

5c. Tertiary Hypotheses: PBMt will alter the microbiome

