**Outcome** **measures**

Group 1 and 2: Outcome measures will be performed at the commencement of the trial before intervention (baseline, week-0), after 4 weeks of treatment, and at the end of the trial (12 weeks of treatment), and at 6-months (3-months of zero intervention wash out). In addition to the physiognomy measurements (weight, girth), motor coordination, balance, cognition, social cognition, smell test, carer diary and self-assessment outcome measures, participants will also be asked to provide faecal and saliva samples (for microbiome analysis) on 2 occasions; 3 samples before treatment begins and 3 samples at the end of the treatment period (12 weeks).

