**12b. Measurement tools used**

- Demographic data
- Physiognomic measurement (height and weight)
- Step test (Appendix 2)
- 10 meter walk test (Appendix 2)
- Spiral test (Appendix 2)
- Montreal Cognitive Assessment (MoCA) test (Appendix 3)
- Timed up-and-go (TUG) (Appendix 2)
- 9-hole peg board (Appendix 2)
- Static balance (feet apart, feet together, eyes open, eyes closed) (Appendix 2)
- Tandem balance (eyes open, eyes closed) (Appendix 2)
- Hand-writing assessment
- PDQ-39 questionnaire (Appendix 4)
- Parkinson’s disease sleep scale (PDSS) questionnaire (Appendix 5)
- Social cognition questionnaires (Appendix 6)
- Carer diary of daily activities (Appendix 7)
- Microbiome analysis (faecal and saliva sample)
- Heart rate variability
- Smell Identification test

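### The half-SD improvement count fixed for every outcome cannot, as written, test whether treatment alters the microbiome

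*Protocol*

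**What the plan says.** **The rule.** Section 13b (Statistical analysis) opens its method with "For each outcome measure, descriptive data (mean, standard deviation) will be calculated". It then derives a minimally important difference of half an SD from the baseline scores, counts participants whose difference between two time points exceeds it in the direction of improvement, and allows those counts to be compared between time points by chi-square. The only comparison across groups that it names is with the Brisbane and Adelaide arms.

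**The microbiome.** It is the last item under 10b (Secondary Outcomes). Objective 3 in Section 4 is about the composition of the gut and oral microbiome. The hypothesis is "5c. Tertiary Hypotheses: PBMt will alter the microbiome". Under Outcome measures, "participants will also be asked to provide faecal and saliva samples (for microbiome analysis) on 2 occasions", namely "3 samples before treatment begins and 3 samples at the end of the treatment period (12 weeks"). Section 12b lists "Microbiome analysis (faecal and saliva sample") and no other laboratory assay of a biological specimen.

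**Cytokines and disease markers.** Section 2 (Background) says that the Sydney trial will assess outcomes "including motor abilities, cognitive function, microbiome changes, cytokine levels and potential Parkinson’s disease marker changes". The same paragraph covers the 2021 stage: "A further cohort will begin treatment in August 2021". Neither item reappears in Section 4, in 10b, under Outcome measures or in 12b.

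**The concern.** A half-SD responder count needs three things: a single number per participant per visit, a known good direction, and something to compare the count with. A clinical scale such as the PDQ-39 supplies the first two. Microbiome composition, as this protocol defines it, supplies none of them.

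At stake is one of the three objectives and the whole of the tertiary hypothesis. If the rule is followed literally, someone must choose an index and a direction after the data are in, and that choice can decide the answer. Without a comparison against sham, a count of changed participants in the active arm also cannot be separated from ordinary variation between two samplings of the same person.

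**Working it through.** The protocol gives no sample-size calculation, alpha or effect size for the microbiome, so there is no figure to reproduce. The main check is a reading of the sections against each other. The arithmetic after it is illustrative.

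**1. What the rule needs and what the protocol supplies**

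| Section 13b needs | Protocol supplies for the microbiome |
|---|---|
| A mean and SD, hence one score | Composition (Section 4); no index named in 10b or 12b |
| A direction of improvement | A non-directional hypothesis (5c) |
| Counts at two or more change intervals | Two occasions, baseline and week 12, so one change per participant |
| A control comparison | None between active and sham in 13b |

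For the clinical measures, visits at week 0, week 4, week 12 and 6 months give three changes from baseline, so counts can at least be set against each other over time. For the microbiome, 2 occasions minus 1 leaves one change, and the chi-square between time points has no second count.

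**2. Illustration: chance crossings if one index were chosen**

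Assumptions, none from the protocol: one scalar index, normal scores, equal SDs at both occasions, no true change, and test-retest correlation r. The SD of change is SD × √(2(1 − r)), so the share passing +0.5 SD is

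P = 1 − Φ(0.5 / √(2(1 − r))).

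- r = 0.5: 0.5/1.000 = 0.500, P = 0.309 (6.2 of 20)
- r = 0.6: 0.5/0.894 = 0.559, P = 0.288 (5.8 of 20)
- r = 0.8: 0.5/0.632 = 0.791, P = 0.215 (4.3 of 20)

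If the three samples per occasion are averaged, and in the best case all disagreement is independent noise between samples, r becomes 3r/(1 + 2r):

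- r = 0.5 becomes 0.75: 0.5/0.707 = 0.707, P = 0.24
- r = 0.6 becomes 1.8/2.2 = 0.82: 0.5/0.603 = 0.829, P = 0.20
- r = 0.8 becomes 2.4/2.6 = 0.92: 0.5/0.392 = 1.275, P = 0.10

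**3. Illustration: the undefined direction**

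Take r = 0.7, so √(2 × 0.3) = 0.775, and let every treated participant shift by 1 SD.

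- Improvement defined in the direction of the shift: 1 − Φ((0.5 − 1)/0.775) = 74.1%
- Improvement defined the other way: 1 − Φ((0.5 + 1)/0.775) = 2.6%

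If instead half the active arm shifts up by 1 SD and half down, the one-direction count is (74.1% + 2.6%)/2 = 38.4% (from unrounded values), against 25.9% with no effect. Even if an arm comparison were added, a test of 20 against 20 at an assumed two-sided 5% level would have about 13% power, although every treated participant had been altered.

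**4. Cytokines and disease markers**

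They are named as outcomes once, in Section 2. The only specimens are faeces and saliva, both labelled for microbiome work. No specimen or assay is assigned to either.

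**The case against.** **The analysis plan may deal with this.** Microbiome methods are usually left to a statistical analysis plan, which may exist. Section 13b is also tentative and speaks of participant scores, which suits clinical scales. Silence would indeed be no finding. But 13b is not silent: it applies its method to each outcome measure, and 10b makes the microbiome one of them.

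**The rule is usable once an index is defined.** True. A named diversity index with a stated direction would supply two of the missing pieces. The protocol names neither, and the single change interval would remain.

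**The replicates could simply be averaged.** This stands. Section 13b neither requires nor forbids it, and averaging lowers the chance crossings, as shown above.

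**Equal chance crossings in both arms would dilute, not create, an effect.** Also true, provided the arms are compared. Section 13b does not say that they will be, a gap that is not peculiar to the microbiome.

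**Stronger readings to resist.** A reader might infer that most participants, or dozens of taxa in each, would be labelled altered by chance. That requires counting change in both directions and testing taxon by taxon. The protocol counts improvement only and plans no taxon-level analysis. A reader might also infer that cytokine and marker results are impossible to produce. Faeces or saliva might be assayed for them; the text supports only that nothing is assigned. That Background paragraph also describes a case-matched design with a different treatment site from Section 6, so the phrase may be carried over from an earlier stage.

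**Conclusion.** The concern holds for the microbiome. As written, Section 13b fixes a method that cannot test hypothesis 5c, because score, direction, second change interval and sham comparison are all missing. That conclusion comes from the text and needs no numerical assumption.

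The percentages only show scale. On the assumptions in the working, roughly one participant in five to three in ten would count as improved with no effect for correlations of 0.5 to 0.8, or about one in ten to one in four with averaged replicates in the best case. The documents give no correlation, so none of these is an estimate for this trial.

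The point should be corrected but is limited in reach: it affects one secondary outcome, Objective 3 and the tertiary hypothesis, not the primary outcome or safety. The cytokine and marker mention is a minor inconsistency to reconcile.

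**What to change.** 1. State in Section 13b that the half-SD rule does not apply to the microbiome.
2. For faeces and saliva separately, compute for each participant the mean community distance between baseline and week-12 samples, minus the mean distance among that participant's own samples from the same occasion. Name the distance metric in advance. Compare this excess distance between active and sham with a permutation test. It needs no direction, and it uses the three samples per occasion to allow for short-term variation.
3. A simpler option would also serve: one pre-specified diversity index per specimen type, with a stated way of combining the three samples and a baseline-adjusted comparison of the arms at week 12.
4. In Section 2, delete the cytokine and disease-marker phrase, or name the specimen and assay for each and add them to 10b, Outcome measures and 12b.

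**Cost.** Items 1 to 3 need protocol wording and some extra analysis of samples already planned. Item 4 costs nothing if the phrase is deleted; keeping it means adding assays.

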**8. STUDY POPULATION**

Two groups of participants will be recruited: 20 participants with PD receiving active intervention (Group 1) and 20 participants with PD receiving sham/placebo intervention (Group 2)

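### Crossing half a baseline SD does not show significant change in one participant; improvers expected by chance are neither set against worseners nor against the sham arm

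*Protocol*

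**What the plan says.** Section 13b of the protocol (Statistical analysis) describes the trial as a series of N=1 studies. It plans a mean and SD for each outcome measure, and then a threshold: "minimally important difference” (MID) scores will be computed based on ½ SD of each measure". The SD meant is the spread between people before treatment, since the measure is said to be "based on the distribution of the participant scores at baseline". The protocol claims that this threshold "provides a sensitive indicator of significant change over time for N=1 case studies".

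The threshold then defines a count: "The number of participants showing improvement (i.e., difference between two time points > MID"). These counts "can be compared between time points with chi-square analyses", and improvers are also to be compared by chi-square with the Brisbane and Adelaide arms, to find the best treatment areas and dose regimens. Section 13b names no comparison of improver counts between active and sham, although section 8 recruits "20 participants with PD receiving active intervention (Group 1) and 20 participants with PD receiving sham/placebo intervention (Group 2").

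Section 13a makes baseline the reference point. The follow-up assessments come "after 4 weeks of treatment, and at the end of the trial (12 weeks of treatment), and at 6-months". No retest reliability or measurement error is given for any outcome.

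**The concern.** A minimally important difference answers whether a change of a given size would matter. Whether one person's observed change exceeds what the same person would show on retest without any change is a different question, and it needs the within-person error of the measure. The between-person SD at baseline does not contain that information. Section 13b treats the first question as if it answered the second.

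At stake is how the improver counts will be read. If everyone who crosses the cut is taken as a significant N=1 change, an inert device will still produce improvers on every imperfectly reliable measure. As many people are expected to cross the same cut downwards, but no count of them is planned. The comparisons that 13b names do not subtract the chance improvers, yet section 15 says the results will guide dose and site of application for a larger trial.

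**Working it through.** **The plan's own figure.** There is none to reproduce: the protocol states no reliability, misclassification rate, significance level or power.

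**Inputs.**
- Cut: 0.5 × SD, with SD the between-person SD at baseline (section 13b).
- Group size: 20 active, 20 sham (sections 8 and 8c).
- Retest correlation r: *assumed*, shown from 0.5 to 0.95.
- *Assumed*: normal scores, no true change, no practice or placebo shift.

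**Formulas.** Let each score be a stable true value plus independent error. The error variance is SD² × (1 − r), so a change between two visits has SD × √(2(1 − r)) as its standard deviation.

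P(labelled improved | no change) = 1 − Φ(0.5 / √(2(1 − r)))

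95% limit for individual change = 1.96 × √(2(1 − r)), in units of the baseline SD

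Example, r = 0.8: √(2 × 0.2) = 0.632; 0.5 / 0.632 = 0.791; 1 − Φ(0.791) = 0.215; 20 × 0.215 = 4.3 people; 1.96 × 0.632 = 1.24.

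| r (assumed) | SD of change | 0.5 ÷ that | Labelled improved | Expected of 20 | 95% limit |
|---|---|---|---|---|---|
| 0.5 | 1.000 | 0.500 | 30.9% | 6.2 | 1.96 SD |
| 0.7 | 0.775 | 0.645 | 25.9% | 5.2 | 1.52 SD |
| 0.8 | 0.632 | 0.791 | 21.5% | 4.3 | 1.24 SD |
| 0.9 | 0.447 | 1.118 | 13.2% | 2.6 | 0.88 SD |
| 0.95 | 0.316 | 1.581 | 5.7% | 1.1 | 0.62 SD |

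These rates are per measure and per follow-up visit. By symmetry the same share worsens by more than the cut.

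**Reliability needed for the claim.** Setting 1.96 × √(2(1 − r)) = 0.5 gives r = 1 − (0.5/1.96)²/2 = 1 − 0.0325 ≈ 0.967.

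**Effect of estimating the SD.** In simulations with the SD taken from 20 participants, the improved share was 26.4%, 21.9% and 13.9% at r = 0.7, 0.8 and 0.9. From 40 participants it was 26.1%, 21.7% and 13.5%. The worsened share matched throughout to within about 0.1 percentage point.

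**Whether the named comparisons remove these improvers.**
- *Between time points.* Under no effect the expected count is the same at each follow-up. Comparing one follow-up with another therefore cannot show whether either count exceeds what chance yields.
- *Against Brisbane and Adelaide.* If each cohort's cut comes from its own baseline SD (an assumption), the chance rate depends on how varied the cohort is. With SD equal to k times the standard error of measurement, P = 1 − Φ(0.5k/√2). For k = 2 this is 24%, for k = 3 it is 14%. With the same measurement error and no effect anywhere, the more homogeneous cohort shows more improvers.

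**The case against.** **A low cut is sensitive, and half an SD is a common importance threshold.** Both are fair. Half an SD may stay as a marker of importance. What fails is the description of crossing it as significant change in an individual.

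**The size rests on an assumed r.** True. Any single percentage would be unsupported, so a range is given. The direction is firmer: the claim fails at the 95% level for every r below about 0.967.

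**The sham arm has the same chance rate.** This stands. A reader might infer that the rule inflates the type I error of an active-versus-sham test. It does not, because chance improvers are expected equally in both arms. The difficulty is that 13b does not name that comparison.

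Other stronger readings that the protocol does not support:
- *That crossing the cut at any visit counts.* Section 13a fixes baseline as the reference, and comparing counts between time points reads as one count per visit.
- *That the direction is undefined.* The count is of participants showing improvement, which is directional, and the better direction is evident from each instrument.
- *That deterioration would be invisible.* The planned means and SDs would show worsening of a group. Only a count of individual worseners is missing.

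**A stricter responder rule might seem the natural repair**, for instance requiring change beyond 1.96 times the SD of change in the sham arm. That would largely fix the sham responder rate by construction and cost much power. With a true shift of 0.5 SD, 20 per arm, a Pearson chi-square test at two-sided 5% and the SD treated as known, exact enumeration gives power of about 7%, 14% and 42% at r = 0.7, 0.8 and 0.9. The existing cut gives 35%, 48% and 75%. Such a rule is not recommended.

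**Conclusion.** The property claimed in 13b is wrong as written. Half the baseline SD can mark an important change, but it does not show significant change in one participant unless the measure is exceptionally reliable (r of about 0.967 or more). With no true change, between about 6% (r = 0.95) and 31% (r = 0.5) of participants would be labelled improved at one follow-up on one measure, or about 1 to 6 of 20. An equal number would worsen uncounted.

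The figures assume normal, stable scores and a retest correlation that the protocol does not report. They describe the meaning of individual and uncontrolled counts, and are not evidence of bias in an active-versus-sham test. Only the protocol was available. If a separate analysis plan compares the counts with sham, the lack of offset falls away, but the significance claim still needs correcting.

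**What to change.** In section 13b:

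1. Delete the claim that half an SD indicates significant change in an individual, and describe it only as an importance threshold.
2. For each measure, classify every participant at week 12 against baseline as improved by more than the cut, unchanged, or worsened by more than the cut.
3. Report the improved count, the worsened count and their difference in each arm.
4. State that the active-arm count will be interpreted only against the sham arm.

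This needs no new data or visits. The cost is a little more tabulation and a less favourable reading of the improver counts.

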**3. AIM OF STUDY**

The main aim of the trial is to intervene in with photobiomodulation, delivered via LED, to determine the efficacy of using this modality to treat the symptoms of Parkinson’s disease and determine if symptoms of Parkinson’s disease are able to be modified to improve quality of life outcomes.

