**11. STUDY OUTCOMES**

**10a. Primary Outcome:** Improved quality of life

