**Appendix 8**

Contingency protocol

In the event that the currently proposed protocol is unable to proceed due to uncontrollable and/or unforeseen restrictions or regulations, the following changes will be implemented to the existing protocol constituting a new contingency protocol.

1. **Study design**
   1. Treatment will consist of home-based (in the participant’s own home) PBMt to the head and nose (either active or placebo treatment), 6 daily treatments per week for 12 weeks. Outcome measures to be supervised and data collected via the use of video link by Specialist Examiners and the Physiotherapists.
2. **Study setting/location**
3. Study location for both treatment outcome measures assessments will be changed to the participant’s own home.
4. **Inclusion criteria**
5. In addition to the inclusion criteria already stipulated, eligible participants will require:

   - Sufficient space (around 9 m^2^) to be able to perform motor assessments.
6. - Stable and sufficiently fast home-based internet connection for uninterrupted video calls and video conferencing.

   - Knowledge (self or carer) of using a phone and/or tablet applications on either IOS or Android platforms.**Study procedure**
7. In the absence of researcher/specialist-directed intervention, to ensure blinding of participants from group allocations and to reduce the change of participants inadvertently realising that they are in the sham, participants will be informed that there are 3 groups rather than 2 (Group 1: receiving red and infra-red light; Group 2: receiving infra-red light only; Group 3: receiving sham). In fact, there will remain to be 2 groups (Group 1: receiving red and infra-red light; Group 2: receiving sham).
8. **Outcome measures**
9. Outcome measures will be performed at the commencement of the trial before intervention (baseline, week-0), then after 2, 4, 6, 8, 10-weeks of treatment, and at the end of the trial (12-weeks of treatment), and at 6-months (3-months of zero intervention wash out).
10. All outcome measures will be conducted and recorded using a combination of self-reported assessment, visual assessment via video link with a specialist examiner (during live video or pre-recording by the participant).

1. **Consent process**
2. All previous in-person appointments during the consent process will now be conducted via video-link. For example:

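### The protocol aims to determine efficacy but fixes no primary measure, deciding visit or active-versus-sham comparison, so a favourable outcome or visit can be chosen after the data are seen

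*Protocol*

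**What the plan says.** Section 3 of the protocol gives the main aim as "to determine the efficacy of using this modality to treat the symptoms of Parkinson’s disease". Section 5 ranks three hypotheses: absence of adverse effects is primary, "5b. Secondary Hypothesis: PBMt will reduce the symptoms of PD" comes second, and a microbiome effect is tertiary.

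Section 11 (items 10a and 10b) gives the primary outcome as "Improved quality of life" and nothing more. The PDQ-39 appears among the secondary outcomes, as a self-assessment, beside motor, balance, cognition, sleep, carer-diary, smell and microbiome measures.

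Section 13a makes baseline the reference for analyses. Section 13b says "it is anticipated that only basic statistical analysis will be performed". For each outcome measure, minimally important difference "scores will be computed based on ½ SD of each measure", and then: "The number of participants showing improvement (i.e., difference between two time points > MID) can be compared between time points with chi-square analyses". The only comparison between groups of participants in 13b is with the Brisbane and Adelaide arms.

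After baseline, the clinic schedule in section 12 measures outcomes "after 4 weeks of treatment, and at the end of the trial (12 weeks of treatment), and at 6-months". Appendix 8 replaces this with "then after 2, 4, 6, 8, 10-weeks of treatment, and at the end of the trial (12-weeks of treatment), and at 6-months".

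**The concern.** An efficacy conclusion needs one measure, one visit and one contrast, fixed in advance. Here the named primary outcome has none of the three. The obvious instrument for it sits in the secondary list, and the primary hypothesis is about something else. The analysis section then treats every outcome alike.

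Two things follow. First, different outcomes and visits can point in different directions, and nothing in the text prevents the favourable one from being put forward as support for hypothesis 5b or as improved quality of life. Second, the comparison that 13b names is between time points. Followed literally, it makes no use of the sham group, so improvement that would also occur without light delivery counts towards benefit.

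Section 2 says the results will be used to argue for a large randomised trial, and section 15 says they will help to power it. Both uses suffer if the supporting result was picked after the fact.

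**Working it through.** The protocol gives no alpha, power or effect size, so there is no stated figure to reproduce. The check asks how often an ineffective device would show at least one significant benefit if the outcomes and visits were left open.

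**Inputs from the protocol**
- Group sizes: 20 active, 20 sham (section 8c).
- Outcomes in 10b: 3 coarse motor + 3 fine motor + 2 balance + MoCA + PDQ-39 + PDSS + carer diary + smell = 13, leaving out the microbiome.
- Changes from baseline: 3 (clinic) or 7 (Appendix 8).
- Tests: 13 × 3 = 39, or 13 × 7 = 91.
- Improver: change greater than 0.5 baseline SD.

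Appendix 2 splits some tests further (three TUG conditions, seven gait variables, two legs on the step test). That would give 13 − 3 + 3 + 7 + 2 = 22 measures. The calculation keeps to 13.

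**Assumptions**
- Two-sided 0.05 per test, so 0.025 in the favourable direction.
- Each test is active versus sham at one visit. Section 13b does not name this test; it is used because it is the one a sham-controlled design calls for.

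**Step 1: equally correlated tests.** The chance of at least one false benefit among K tests is 1 − E[P(Z < 1.96 | F)^K], averaged over a common factor F that gives correlation ρ.

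| K | ρ = 0.3 | ρ = 0.5 | ρ = 0.7 | ρ = 0.8 |
|---|---|---|---|---|
| 39 | 39.9% | 28.6% | 18.6% | 13.9% |
| 91 | 56.0% | 39.0% | 24.3% | 17.5% |

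Counting significant results in either direction, the ρ = 0.5 values are 57% for 39 tests and 76% for 91. Those figures include apparent harm, so they do not measure false benefit. Independence would give 1 − 0.975^39 = 63% for 39 tests, but outcomes in the same patients are correlated, so that is a ceiling for this model.

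**Step 2: simulation of the half-SD improver rule.** 20 versus 20, no effect, Pearson chi-square, correlation between outcomes 0.3–0.7, retest correlation 0.7–0.9. Chance of at least one false benefit:

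| | Uncorrected | Continuity-corrected |
|---|---|---|
| 39 tests | 38–54% | 11–30% |
| 91 tests | 61–75% | 24–49% |

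**Step 3: combined range.** Taking the lowest and highest value across both steps gives about 11–54% for three visits and about 18–75% for seven. Even the lowest is more than four times nominal (11 / 2.5 = 4.4).

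**Step 4: improvers when nothing happens.** With no effect and retest correlation r, the chance of exceeding the threshold is 1 − Φ(0.5 / √(2(1 − r))). This is 13.2% at r = 0.9, 25.9% at r = 0.7 and 30.9% at r = 0.5. In an arm of 20 that is 20 × 0.132 = 2.6 to 20 × 0.309 = 6.2 improvers from measurement variation alone, before any placebo or practice effect. A count of improvers without the sham arm beside it says little about the device.

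**Step 5: after the fix.** One outcome, one visit, active versus sham, is tested at its nominal 2.5% for benefit.

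**The case against.** The strongest reply is that the protocol does rank things. A reader might infer that there is no hierarchy at all, and that is wrong: section 5 orders the hypotheses and section 11 separates primary from secondary outcomes. If quality of life were honoured as the only deciding outcome, three open visits would give a false-benefit rate of about 6% (step 1 formula, K = 3, ρ = 0.5), far below the ranges above. What remains is that the ranking cannot decide anything, because the primary outcome has no instrument, visit or contrast and does not match the primary hypothesis.

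A reader might also infer that any pair of visits may be compared, and count every pair. Section 13a makes baseline the reference, so only the changes from baseline are counted here. The wording in 13b is also permissive: counts may be compared; it does not say that every outcome will be tested.

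Multiplicity rules and exploratory labels may sit in a statistical analysis plan that is not shown, and their absence is not the point. The primary measure, its visit and the treatment contrast belong in the protocol, and here they are left open or inconsistent.

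Finally, the trial is described as Phase 1 and proof-of-concept, and a later randomised trial would test any chance finding. That lowers the stakes. It does not remove the stated efficacy aim, and it labels no analysis as exploratory.

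**Conclusion.** The point holds in this form: the protocol states an efficacy aim but fixes no measure, visit or active-versus-sham contrast that would decide it, and the comparison it names is between time points.

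The false-benefit chance is about 11–54% on the clinic schedule and about 18–75% under Appendix 8, against 2.5%. These figures rest on an assumed two-sided 0.05, on 13 outcomes all being open to selection, on assumed correlations, and on active-versus-sham tests that 13b does not itself specify. They do not measure the added bias from within-group comparisons.

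A reader might conclude that an ineffective device would probably show a significant benefit. The clinic schedule does not support that: most of its range lies below one half, and it passes one half only without continuity correction and with low correlation. Under Appendix 8 the answer depends on the same choices. What holds throughout is inflation well above nominal.

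**What to change.** - **10a and 10b:** name the PDQ-39 as the primary measure and move it out of the secondary list.
- **13b:** state that change in PDQ-39 from baseline to week 12, active versus sham, is the single comparison that supports an efficacy conclusion, and give its significance level (for example two-sided 0.05). Week 12 occurs in both the clinic and the Appendix 8 schedules, so say that the same visit applies under either.
- **13b:** define change at every visit as change from baseline, in place of an open pair of time points.
- **13b:** report all other outcomes and visits as supportive or exploratory estimates with 95% intervals and no efficacy claim.
- **Section 5:** align the hypotheses with this primary outcome.

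The cost is a few sentences, with no added patients, visits or measurements. The downside is that an isolated favourable result on another outcome or visit can no longer be presented as efficacy.
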